
#### 2.2.2. Sample Size

With reference to an exploratory pilot study in which a sample size of 12 per group was recommended [26], the sample size of this trial was 24 participants (12 per group). This is the first randomized controlled trial to investigate the efficacy, safety, and economic evaluation of WBGCT for UACS-induced chronic cough [18]. Considering a 20% dropout rate, 30 participants (15 per group) will be recruited.

#### 2.2.3. Recruitment

Participants will be recruited from regular promotions through mass media, such as newspaper leaflets, daily newspapers, and advertising posters and brochures displayed in the hospital’s outpatient departments. When the recruitment of participants is delayed during the clinical trial, local advertisements will be displayed (subway, bus, and apartment notice boards). Cooperation with patients with chronic cough from online communities, local groups, or societies will also be considered.

### 2.3. Interventions

#### 2.3.1. WBGCT Group

Participants in the WBGCT group will be instructed to take three packs of the investigational medicine (WBGCT) before or between meals three times per day for 2 weeks. WBGCT consists of six medicinal herbs: Ephedrae Herba 3.75 g, Zizyphi Fructus 0.67 g, Gypsum Fibrosum 1.25 g, Atractylodis Rhizoma 2.50 g, Glycyrrhizae Radix et Rhizoma 1.25 g, and Zingiberis Rhizoma Recens 0.83 g, which is manufactured as light brown granules. WBGCT will be purchased from the Kyungbang Pharm Corporation (Incheon, Republic of Korea), a company that has obtained authorization from the Korea Good Manufacturing Practice.

#### 2.3.2. Control Group

Participants in the control group will be instructed to take three packs of active comparator (SCRT) before or between meals three times per day for 2 weeks. SCRT consists of eight medicinal herbs: Ephedrae Herba 0.3 g, Paeoniae Radix 0.51 g, Pinelliae Tuber 0.47 g, Schisandrae Fructus 0.55 g, Cinnamomi Ramulus 0.04 g, Asiasari Radix et Rhizoma 0.18 g, Glycyrrhizae Radix et Rhizoma 0.34 g, and Zingiberis Rhizoma 0.28 g, which is manufactured as brown granules. SCRT will be purchased from the Kyungbang Pharm Corporation. The ingredients and compositions of the WBGCT and SCRT are listed in Table 2.

### 2.4. Outcome Measures

#### 2.4.1. Primary Outcome Measures: Cough Symptom Score (CSS)

The CSS is a rating scale for cough frequency during the day and at night. The score for each question ranges from 0 to 5 (with the total score ranging from 0 to 10) [27]. CSS has been used to assess the severity of cough and the efficacy of therapy in many studies on cough [28,29]. In this study, the Korean version of the CSS will be used, which has proven its validity and clinical utility, as well as acceptable repeatability and responsiveness to changes in patients with chronic cough [30]. Participants will evaluate their cough symptoms twice a day using a cough diary (assessment of daytime CCS from 08:00 to 20:00 at 8 PM and assessment of nighttime CSS from 20:00 to 08:00 at 8 AM). CSS will be assessed at visits 1, 2, 3, and 4.

#### 2.4.2. Secondary Outcome Measures

(1)Cough Visual Analog Scale (VAS).

The VAS evaluates cough severity and frequency. The score ranges from 0 to 10 (0 means “no cough” and 10 means “cough as severe as it could possibly be”) [31]. The VAS will be assessed on visits 2, 3, and 4.

(2)Nasal Discharge Score (NDS)

The NDS assesses the severity of two symptoms: nasal discharge (anterior nasal discharge score) and mucous globus sensation in the back of the throat (posterior nasal discharge score), ranging from 0 to 3 (0 = none; 1 = mild; 2 = moderate; 3 = severe) [6]. Since the symptoms of UACS include nasal symptoms, such as nasal discharge and rhinorrhea, symptoms related to nasal discharge will be assessed using the NDS in this trial [6]. The NDS will be evaluated on visits 2, 3, and 4.

(3)Questionnaire of Clinical Symptoms of Cough and Sputum (QCSCS)

The QCSCS is developed from the Clinical Asthma Measurement Scale in Oriental Medicine-V (CAMSOM-V) in the Traditional Korean Medicine Clinical Practice Guidelines for Antitussives and Expectorants, remodeled for cough and sputum [32,33]. The items for the QCSCS are as follows: (1) cough (frequency, intensity, and sensitivity), (2) sputum (frequency, volume, difficulty in coughing, appearance, and color), (3) activities of daily living, and (4) nighttime sleeping. Each item is measured using a 4-point scale, with a maximum total score of 40 points. The QCSCS will be assessed on visits 2, 3, and 4.

(4)Leicester Cough Questionnaire-Korean version (LCQ-K)

The LCQ-K evaluates the quality of life of patients with a cough and consists of 19 items divided into three parts: psychological, social, and physical aspects. Each item ranges from 1 to 7, with higher scores indicating a better quality of life. Previous studies have shown a correlation between the LCQ score and the severity of cough symptoms. The LCQ-K has been translated into Korean and verified for its validity and reliability [34,35]. The LCQ-K will be assessed on visits 2, 3, and 4.

(5)Integrative Medicine Outcome Scale (IMOS) & Integrative Medicine Patient Satisfaction Scale (IMPSS)

The IMOS evaluates symptom improvement. In this trial, the IMOS will be assessed by the investigators. The IMPSS is a rating scale used to assess treatment satisfaction of patients [36]. The scores on both scales range from 1 to 5. The IMOS and IMPSS will be evaluated on visits 3 and 4.

(6)5-level EuroQol 5-Dimensional Questionnaire (EQ-5D-5L)

The EQ-5D-5L is a self-rating questionnaire that evaluates the quality of life of the general population or patients with various diseases and consist of five dimensions (mobility, self-care, usual activities, pain/discomfort, and anxiety/depression), each with five levels. In addition, participants rate their health by marking a vertical VAS labeled number from 0 to 100 (100 means “the best health you can imagine” and 0 means “the worst health you can imagine”) [37]. The EQ-5D-5L will be evaluated on visits 2, 3, and 4.

#### 2.4.3. Exploratory Outcome Measures: Pattern Identification for Chronic Cough Questionnaire (PICCQ)

The PICCQ is used to identify patterns of chronic cough in each participant and is conducted at baseline of the trial. Chronic cough is classified into five patterns according to its signs and symptoms: cold wind, phlegm turbidity, fire-heat, lung deficiency, and kidney yang deficiency [38]. These pattern identifications are important diagnostic criteria used to determine appropriate medications and other therapies in Korean Medicine. Thus, we will investigate the correlation between pattern identification and the effectiveness of WBGST and SCRT.

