## 2. Methods

### 2.1. Study Design

This is a randomized, double-blind, active-comparator-controlled, parallel, exploratory clinical trial to evaluate the efficacy, safety, and economic feasibility of WBGCT for UACS-induced chronic cough. Thirty participants will be recruited for this trial and randomly assigned to the WBGCT and control groups in a 1:1 allocation ratio. This trial consists of screening, 2-week treatment, and 2-week observation periods. The medications will be administered three times a day for 2 weeks. The detailed study design is summarized in Figure 1 and Table 1.

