### 2.7. Assignment of Interventions

#### 2.7.1. Allocation

The participants are allocated according to blocked randomization without stratification. A randomized allocation sequence will be assigned to each group based on a computer-generated random number table created by an independent statistician using SAS version 9.4 statistical software (SAS Institute. Inc., Cary, NC, USA). After consent to the clinical trial, the participants’ identification code will be assigned to those who meet the inclusion and exclusion criteria. The participants will be allocated to the WBGCT and control groups at an allocation ratio of 1:1. The randomization table will be retained separately by the independent statistician to maintain blinding. The assignment of participants will be conducted according to the assignment table generated by a random assignment method that can be specifically planned and reproduced in advance. According to the randomized assignment table, the participants’ identification codes will be kept in an opaque envelope and a cabinet with double locks.

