## 5. Conclusions

This study aims to demonstrate the effects of WBGCT on UACS-induced chronic cough. As WBGCT has been used widely for respiratory diseases over a long period of time with few side effects, WBGCT is expected to be a safe and effective agent for UACS-induced chronic cough. Moreover, considering that our intervention is Korean medicine, we used pattern identification to obtain additional information on whether certain patterns of patients respond better than others to the treatment. Additionally, we perform an economic evaluation of WBGCT compared to SCRT, expecting the expansion of newly applied health insurance-covered herbal formulas. Our study will support the efficacy, safety, and economic feasibility of WBGCT and provide evidence for its clinical use.

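### A correlation between cough pattern and outcome cannot show which patterns respond better to treatment; only a pattern difference in the randomised WBGCT-minus-SCRT contrast bears on that, and only relative to SCRT

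*Protocol article*

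**What the plan says.** Section 2.4.3 lists the pattern questionnaire (PICCQ) as an exploratory measure taken at baseline. It states that "Chronic cough is classified into five patterns according to its signs and symptoms" and that "we will investigate the correlation between pattern identification and the effectiveness of WBGST and SCRT" (WBGST is evidently a misprint for WBGCT). The Conclusions give the purpose: additional information on "whether certain patterns of patients respond better than others to the treatment".

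Section 2.1 has participants "randomly assigned to the WBGCT and control groups in a 1:1 allocation ratio". Section 2.2.2 sets 24 participants (12 per group) and continues: "Considering a 20% dropout rate, 30 participants (15 per group) will be recruited". Section 2.7.1 adds: "The participants are allocated according to blocked randomization without stratification". The Discussion concedes that there is no placebo group and that the sample is small, but relates both to the overall effect of WBGCT. It says nothing about how pattern results may be read.

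**The concern.** The analysis described in section 2.4.3 associates a baseline characteristic with outcome. The purpose in the Conclusions concerns effect modification: whether the product does more for some patterns than for others. The first does not deliver the second.

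An effect of SCRT cannot itself be a WBGCT-minus-SCRT difference, so the effectiveness of each product most naturally means change from before to after treatment under that product. Such change includes what would have happened anyway. Patterns defined by signs and symptoms may differ in natural course and in starting severity. Entry also requires minimum daytime and nighttime cough scores (section 2.2.1), so some regression to the mean is to be expected, and its size may differ between patterns.

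If the two sections are followed as worded, a pattern with a better prognosis could be described as one that responds better to a product. The planned next trial could take that up as a lead.

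**Working it through.** **1. The plan's own figure.** Section 2.2.2 inflates 24 for 20% dropout: 24/(1 - 0.20) = 30, and 12/0.80 = 15 per arm. This reproduces exactly.

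**2. What each comparison estimates.** For pattern k and product a, write the mean change as c(k) + e(k,a). Here c(k) is the change that would occur without effective treatment (natural course plus regression to the mean), and e(k,a) is the effect of product a in pattern k.

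- Pattern k against pattern l under WBGCT: [c(k) - c(l)] + [e(k,W) - e(l,W)]. The first bracket is prognosis, and no arm in the trial estimates it.
- The same comparison pooled over two equal arms: [c(k) - c(l)] plus the average of the two effect differences. Prognosis is still there.
- Difference between patterns in the WBGCT-minus-SCRT contrast: [e(k,W) - e(l,W)] - [e(k,S) - e(l,S)]. The c terms cancel through randomisation. What remains is differing response relative to SCRT. The Discussion says SCRT has not been studied in UACS, so its effect by pattern cannot be taken as zero or as known.

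**3. Size of the false signal.** Simulation with 4,000 runs per setting. Assumptions: residual SD 1, patterns split as evenly as possible, an identical treatment effect in all patterns, c(k) equal to -1, -0.5, 0, 0.5 and 1 SD, and two-sided alpha 0.05.

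| Spread of natural course | Within-arm test of pattern, 12 / 15 per arm | Pattern-by-arm test, 12 / 15 per arm |
|---|---|---|
| None | 5.5% / 4.7% | 5.2% / 4.7% |
| -1 to +1 SD | 27% / 38% | 5.0% / 4.7% |
| -2 to +2 SD | 83% / 95% | 5.8% / 5.9% |

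The spreads are assumptions, since the article gives no outcome data by pattern. They show the mechanism and its possible size.

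**4. How much the valid contrast can say.** Five patterns by two arms make ten cells: 30/10 = 3 and 24/10 = 2.4 people on average. With even cells of m people and SD 1, a two-pattern contrast has SE = sqrt(4/m).

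- 12 per arm: sqrt(4/2.4) = 1.29 SD; 95% half-width 2.145 × 1.29 = 2.8 SD (t, 14 df).
- 15 per arm: sqrt(4/3) = 1.15 SD; 95% half-width 2.086 × 1.15 = 2.4 SD (t, 20 df).

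Empty cells: with equally common patterns (assumption), the chance that all five appear in one arm of n is 1 - 5(0.8^n) + 10(0.6^n) - 10(0.4^n) + 5(0.2^n).

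- n = 15: 0.829, so the chance of at least one empty cell among ten is 1 - 0.829² = 0.31.
- n = 12: 0.678, so it is 1 - 0.678² = 0.54.
- With an assumed uneven split of 40/25/15/10/10, simulation gives 0.70 (15 per arm) and 0.84 (12 per arm).

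Collapsing helps only in part. One pattern holding a fifth of participants against the other four has SE sqrt(2(1/3 + 1/12)) = 0.91 SD with 15 per arm, a half-width of about 1.8 SD (1.96 × SE). With 12 per arm the half-width is about 2.0 SD.

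**The case against.** The strongest reply is that the article does not fix the model. Section 2.4.3 names no within-arm test and no change score, and section 2.9 describes no method for the PICCQ. The model for an exploratory measure is normally left to the full protocol or SAP. This stands: a reader might infer that the plan commits to correlations inside each arm, but that is only the natural reading of the sentence. The point does not depend on it, because a correlation pooled over arms carries the same prognostic term. Section 2.9 also allows covariates that can affect chronic cough. Adjusting for baseline severity would remove part of the problem, but not differences in natural course.

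Three further inferences are tempting and not supported.

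- That without a placebo the trial can show nothing about differing response. It randomises between two products, so differing response relative to SCRT can be estimated, if poorly.
- That the trial sets out to establish which patterns respond better. The measure is labelled exploratory, and the Conclusions speak only of additional information.
- That the small cells are themselves the fault. In a pilot with acknowledged limits they are not; they matter because they restrict what the valid contrast can deliver.

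Nor does the article say that treatment will be chosen from this analysis. Its remark that patterns guide medication is background on Korean Medicine.

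**Conclusion.** The point holds as a mismatch between a stated analysis and its stated interpretation. A pattern-outcome association is prognostic; reading it as better response to a product is not supported without the randomised contrast by pattern. The limits conceded in the Discussion do not cover this reading, and a fuller model in an SAP would still leave the wording of the two sections to be corrected.

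The algebra needs only randomisation and the absence of an untreated arm. The false-signal rates depend on the assumed spread of natural course, and the precision figures on even cells and SD 1. Importance is minor: the analysis is exploratory and the primary comparison is not affected.

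**What to change.** In section 2.4.3, replace the correlation with a descriptive table by pattern and arm: counts, baseline CSS and baseline-adjusted change. Base any statement on differing response on the pattern-by-arm (WBGCT-minus-SCRT) contrast with its confidence interval. Fix in advance a rule for collapsing sparse patterns that does not use outcomes, and label the contrast descriptive because 2.4 to 3 people per cell are expected on average. Which grouping to use is for the trial team; none will be precise at this size.

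In section 2.4.3 and the Conclusions, state that associations between pattern and outcome are prognostic and will not be reported as one pattern responding better to a product.

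The cost is analysis and wording only; recruitment, visits and data collection stay as they are. What is given up is a five-pattern statement on response, which the design cannot support.

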### 2.5. Safety Assessment

For the safety assessment, adverse events (AEs), vital signs, electrocardiograms, and clinical laboratory tests (complete blood count, liver function test, and urine analysis) will be assessed. AEs are harmful and unintended signs, symptoms, and diseases in patients taking investigational drugs, which do not necessarily imply a causal relationship with the investigational drugs. Vital signs and AEs will be assessed at every visit after the investigational medications are administered (visits 2, 3, and 4). The investigators will record the date of onset, severity, results of AEs, action taken against investigational medications, causal relationship between AEs and investigational medications, other suspected medicines, and treatments for AEs. When AEs occur, the principal investigator should conduct continuous follow-up until they disappear, or the patients are in a stable condition. All serious AEs will be reported to the principal investigator within 24 h.

### 2.6. Economic Evaluation

The primary economic endpoint is the incremental cost-utility ratio (ICUR) calculated at every visit using the EQ-5D-5L. The secondary economic endpoint is the incremental cost-effectiveness ratio (ICER) calculated at every visit using the variables for clinical effectiveness. A cost evaluation will be performed using micro-costing based on data, including survey results, medical records, and administration data, while gross costing will be conducted as needed. Cost assessments will be performed using surveys conducted on visits 2, 3, and 4. For participants who dropped out of the trial early, the costs until the investigational medication ended will be collected.

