## Abstract

Upper airway cough syndrome (UACS) is a common cause of chronic cough characterized by upper airway symptoms, including nasal discharge and throat discomfort. Empirical treatments for UASC-induced chronic cough, such as first-generation antihistamines, have been used; however, the long-term use of these medicines has adverse effects. Therefore, we evaluate the efficacy, safety, and economic feasibility of Wolbigachul-tang (WBGCT), an herbal medication for UASC-induced chronic cough. This is a randomized, double-blind, active-comparator-controlled, parallel, and exploratory clinical trial. Thirty patients with UASC-induced chronic cough will be recruited and randomly allocated to the WBGCT and control groups in a 1:1 allocation ratio. The investigational medicine will be administered three times per day for 2 weeks (3 g of WBGCT at a time). The primary outcome measure is the cough symptom score measured at screening, before starting the trial, and after 2 and 4 weeks. Secondary outcome measures include the cough visual analog scale, nasal discharge score, questionnaire of clinical symptoms of cough and sputum, Leicester cough questionnaire-Korean version, integrative medicine outcome scale, integrative medicine patient satisfaction scale, and 5-level EuroQol 5-dimensional questionnaire, which will be assessed before starting the trial and after 2 and 4 weeks. This study aims to investigate the efficacy, safety, and economic feasibility of WBGCT in the treatment of chronic cough. Therefore, the results of this trial provide evidence for the application of WBGCT in the treatment of UACS-induced chronic cough.

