Descriptive statistics for each group regarding demographic characteristics and baseline data will be presented. Continuous variables will be expressed as means and confidence intervals, and an independent *t*-test or Wilcoxon rank-sum test will be performed depending on their normality. Categorical variables are expressed as frequencies and percentages, and χ2 test or Fisher’s exact test will be conducted. The primary outcome measures will be analyzed using the mixed effect model repeated measure (MMRM), setting each group and visit as a fixed effect and participants as a random effect. If necessary, the fixed effects will include variables with significant differences in demographic characteristics or variables that can affect chronic cough. Analysis of the primary outcome measures are expressed as mean and 95% confidence interval (CI). Among the secondary outcome measures, CSS scores for 4 weeks against baseline and cough VAS, NDS, LCQ-K, and QCSCS scores will be analyzed using the same methods as the primary outcome measure. Depending on normality, Student’s paired *t*-test or Wilcoxon signed-rank test will be used to analyze differences in scores before and after treatment. The IMOS and IMPSS scores at 2- and 4-week intervals will be analyzed using Fisher’s exact test. Repeated-measures analysis of variance (RM ANOVA) will be used to compare the differences in the changes in CSS score trends between the groups, and Dunnett’s procedure for multiple comparison correction will be used. When performing the Student’s paired *t*-test, Wilcoxon signed-rank test, or RM ANOVA, a missing data will be substituted with Last Observation Carried Forward (LOCF) or Multiple Imputation (MI).

A safety evaluation will be conducted on participants who receive Interventions at least once. The number of AEs between the groups will be compared using Fisher’s exact test. Differences in laboratory test variables before and after treatment will be analyzed using the Student’s paired *t*-test or Wilcoxon signed-rank test.

Economic evaluations will be performed from both social and limited social perspectives. In sensitivity analysis, the available variables will be analyzed using a one-way sensitivity analysis with a tornado diagram. If necessary, a probabilistic sensitivity analysis will be conducted using the distribution and representative values of the variables.

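### Costs for early dropouts are collected only until medication ends while others are costed to week 4, and the primary ICUR is not tied to one time point

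*Protocol article*

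**What the plan says.** Section 2.6 defines the economic endpoints: "The primary economic endpoint is the incremental cost-utility ratio (ICUR) calculated at every visit using the EQ-5D-5L", and "The secondary economic endpoint is the incremental cost-effectiveness ratio (ICER) calculated at every visit using the variables for clinical effectiveness". On data collection it says "Cost assessments will be performed using surveys conducted on visits 2, 3, and 4". Section 2.4.2 gives the same visits for the utility measure: "The EQ-5D-5L will be evaluated on visits 2, 3, and 4". Table 1 places visit 2 at time 0 (allocation), visit 3 at week 2 and visit 4 at week 4.

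Early dropouts have their own rule in 2.6: "For participants who dropped out of the trial early, the costs until the investigational medication ended will be collected". Section 2.1 gives two weeks of treatment followed by two weeks of observation.

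Other parts of the plan bear on this:
- The main analysis set in 2.9 rests on intention-to-treat principles. No separate set is named for the economic evaluation.
- Section 2.9 takes social and limited social perspectives.
- Section 2.5 has adverse events followed until they resolve or the patient is stable, and their treatment recorded.
- The imputation rule in 2.9 (LOCF or multiple imputation) is attached to the paired tests and RM ANOVA. It does not mention costs.
- The committed economic sensitivity analysis is one-way, with "If necessary, a probabilistic sensitivity analysis will be conducted using the distribution and representative values of the variables".

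**The concern.** There are two separate problems.

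**Unequal costing windows.** The length of cost follow-up depends on whether the participant stays in the trial. People who stop early may have later costs unlike those of people who stay, for example other care for the cough or lost time, and a social perspective counts both. An analysis plan cannot fully repair this afterwards, because imputation would have to borrow from participants who did not withdraw. Incremental cost is the numerator of both the ICUR and the ICER, and the Introduction and Conclusions link the economic result to insurance coverage. The Introduction reports palpitation and insomnia with WBGCT and describes the safety of SCRT as demonstrated. Unequal withdrawal is therefore plausible, although the article does not predict it.

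**No single primary ratio.** A ratio computed visit by visit gives several values of one primary economic endpoint, with no statement of which one counts. If weeks 2 and 4 point in different directions, the plan does not say which to report as primary.

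**Working it through.** **1. The plan's own figure.** Section 2.2.2 has 12 evaluable per group and 20% dropout: 12/(1 − 0.20) = 15 per group, and 24/0.80 = 30 in all. This reproduces. Expected dropouts are 0.20 × 15 = 3 per group, or 6 in total.

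**2. The uncosted interval.** Let a dropout stop medication at week t. Treatment lasts 2 weeks, so t ≤ 2, and 4 − t weeks (at least 2 of the 4) fall outside cost collection.

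**3. Apparent gap between arms.** Assume every participant accrues the same cost each week and uncollected costs are entered as zero; the article states neither. With d dropouts of 15, mean observed cost in weekly units is [(15 − d) × 4 + d × t]/15. As a share of the full 4-week cost, the gap between arms A and B is −(dA − dB)(4 − t)/(15 × 4).

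| Dropouts, A vs B | t = 0.5 | t = 1 | t = 2 |
|---|---|---|---|
| 3 vs 3 | 0% | 0% | 0% |
| 3 vs 1 | −11.7% | −10.0% | −6.7% |
| 3 vs 0 | −17.5% | −15.0% | −10.0% |
| 5 vs 1 | −23.3% | −20.0% | −13.3% |

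For example, for 3 vs 1 at t = 0.5, the arm means are 49.5/15 = 3.30 and 56.5/15 = 3.77, a difference of 0.47, and 0.47/4 = 11.7%.

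**4. Is that gap a bias?** This depends on what dropouts cost after stopping. Let r be their weekly cost after withdrawal relative to before. For 3 vs 1 at t = 1, the true gap is 2 × (3r − 3)/60 = 10% × (r − 1), while the observed gap is always −10%.
- r = 0: true gap −10%, no bias.
- r = 1: true gap 0%, error of 10 percentage points.
- r = 2: true gap +10%, so the sign is reversed.

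**5. How often would dropout be unequal?** Treat the two arms as independent Binomial(15, 0.20) counts. Chance alone gives a difference of at least 2 dropouts in 49% of trials and at least 3 in 25%, before any true difference in tolerability.

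**6. What every visit can mean.**
- Visit 1 has neither EQ-5D-5L nor a cost survey, so no ratio is possible there.
- Visit 2 is week 0. The Abstract lists EQ-5D-5L among secondary measures "which will be assessed before starting the trial and after 2 and 4 weeks", which makes visit 2 the baseline, although section 2.5 describes vital signs and adverse events at "every visit after the investigational medications are administered (visits 2, 3, and 4". At a pre-dose visit, randomisation makes the expected cost difference and the expected utility difference both zero, so the ratio has no meaning.
- Visits 3 and 4 each give a valid ratio, and nothing ranks them.

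**The case against.** The best defence is that the dropout sentence says only what will be collected. It does not say the remaining weeks count as zero, and the handling of missing costs may sit in a full protocol or analysis plan that is not shown. This stands as far as direction and size go. A reader might infer that the arm with more dropouts will look cheaper. The article does not support that as a fact: it needs unequal dropout (or later costs that differ by arm), later costs above zero, and uncollected costs treated as zero. What survives is that the collection rule is written down, and data never collected limit any later method.

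A reader might also infer that adverse-event costs are lost. Section 2.5 records treatment of adverse events, and 2.6 draws on medical records as well as surveys, so some of this information may exist. The fair criticism is that the cut-off in 2.6 is not reconciled with that follow-up. Even accrual is doubtful too: drug cost that a dropout never incurs is not missing. Nor is the share of cost missing within one arm the bias, since equal shares cancel in the increment.

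On timing, every visit cannot be wholly literal, and each post-baseline visit is the ordinary reading. No sentence commits to a week-0 ICUR. That objection removes the week-0 ratio as a firm charge but leaves weeks 2 and 4 unranked.

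Finally, it is tempting to blame the visit-by-visit wording for an unstable ratio. Instability at weeks 2 and 4 comes from about 12 evaluable participants per group and a four-week horizon. A single ICUR would share it, and the Discussion already lists the small sample and short period as limitations. Much of the detail of uncertainty methods properly belongs in an economic analysis plan.

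**Conclusion.** The concern holds in limited form. Section 2.6 sets a shorter costing window for early dropouts than for everyone else. That is at odds with intention-to-treat principles and the social perspective, and it can bias incremental cost when dropout or post-withdrawal cost differs by arm. Under the assumptions shown (3 vs 1 dropouts of 15, stopping at weeks 0.5 to 2, even accrual, uncollected costs as zero) the spurious gap is about 7–12% of the four-week cost. It is 0% with equal dropout and equal later costs. The documents give no cost data, so this illustrates the mechanism and does not forecast the result.

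Independently, the primary economic endpoint yields at least two unranked ratios, and a meaningless third if read literally. The trial is exploratory and its primary outcome is the cough symptom score, so both are cheap improvements rather than threats to the main result.

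**What to change.** In 2.6, replace the dropout rule with wording such as: *costs and EQ-5D-5L will be collected to week 4 for every randomised participant, whether or not medication continues, using the existing survey; intervals that cannot be obtained will be treated as missing, not as zero cost.* State how adverse-event treatment recorded under 2.5 feeds into the costs.

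Also in 2.6, use week 0 only as baseline and define one primary ICUR over weeks 0–4. Any week-2 ratio becomes descriptive. In 2.9, report incremental cost and incremental QALYs separately, with bootstrap intervals, alongside the ratio.

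The cost is at most one follow-up survey contact per dropout, about six people (0.20 × 30), and a little more analysis. Participants who refuse further contact stay missing, so the change reduces the problem without removing it. It does not make the ratio precise at this sample size; the intervals would show that openly.
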